### Treatment arms

#### Psychosomatic therapy

Psychosomatic therapy is administered by psychosomatic therapists. These are exercise and physical therapists with a special interest in MUS and registered with the Dutch Association for Exercise Therapists [15] and the Dutch Association for Psychosomatics in Physical Therapy [16], respectively. Psychosomatic therapy has been developed using the well-known concept of the biopsychosocial model in which illness is viewed as a result of interacting mechanisms at the biomedical, interpersonal and environmental levels. It implies that patients’ symptoms, illness beliefs, anxiety, concerns, illness behaviour and social environment are addressed. Psychosomatic therapy is a multi-component, stepped-care and tailored approach and includes the following elements: (1) psycho-education, (2) relaxation therapy and mindfulness, (3) cognitive behavioural approaches and (4) activating therapy. In the psychosomatic therapy sessions the therapist together with the patient explores somatic symptoms and integrates the physical, cognitive, emotional, behavioural and social dimensions of the symptoms presented. During the therapy, underlying beliefs and psychosocial factors which influence the perceived somatic symptoms, are identified in order to give patients (experienced) insight into the interaction of these factors with the somatic symptoms. The aim of the intervention is to improve functioning. The assumed working mechanism of the psychosomatic intervention comprises of three elements, i.e. empowerment of the patients to regain control over their own health, stimulating self-regulated ability and monitoring on behavioural change. Figure 3 presents the graphical representation of these assumed working mechanism of psychosomatic therapy.

**Fig. 3 Fig3:**
[figure not shown]
Graphical representation of the assumed working mechanism of psychosomatic therapy. **RET* Rational Emotive Therapy*, NLP* Neuro Linguistic Programme*, ACT* Acceptance and Commitment Therapy

For this study a standardised treatment protocol is developed, but the therapists are allowed to change the intensity, frequency and order of the elements in order to deliver personalised care. The psychosomatic therapists will receive an intensive training, an accredited e-learning and two meetings of 4 h each, focussed on MUS, information about the study and the standardised treatment protocol. The patient will not be restricted in seeking other care.

#### Care as usual

Patients in the control group will receive usual care provided by the GP and other health care professionals, with no restrictions. The guideline on the management of MUS of the Dutch College of General Practitioners [30] describes the usual care. It recommends GPs to focus on the exploration of the symptoms, and on related cognitions, emotions and behaviour, and apply psychoeducation, monitoring, and, when necessary, to refer a patient to a physical therapist, a mental health nurse-practitioner or a psychologist.

### Outcome measures

#### Primary outcome

In order to estimate the primary outcome of the treatment we will measure patients’ level of specific functioning and disability measured with the PSFS. The PSFS is a self-reported, thoroughly validated, responsive measurement instrument for up to three individual activities for which patients perceive limitations rated on an 11-point numeric rating scale (NRS) ranging from 0–10 (0 representing ’impossible‘ and 10 ’not a problem at all‘) [24, 31–33]. We will measure mean change from baseline at 4 and 12 months’ follow-ups.

#### Secondary outcomes

Secondary outcomes will be severity of physical and psychosocial symptoms, physical and mental health status, quality of life, health anxiety, illness behaviour and illness beliefs.

Perceived symptom severity is measured on a NRS (range 0–10; 10 represents most severe symptoms) [34].

Patients’ self-rated psychosocial symptoms are measured with the Four Dimensional Symptom Questionnaire (4DSQ). The 4DSQ consists of 50 items with four subscales: distress, depression, anxiety and somatisation. The score for individual items are rated on a five-point Likert scale (no (0), sometimes (1), regularly, frequently or continuously (2)) [35]. Distress and somatisation scores range from 0 to 32 (low: 0–10; moderate: 11–20; high: 21–32), subscale anxiety scores range from 0 to 24 (low: 0–7; moderate: 8–12; high: 13–24) and subscale depression scores range from 0 to 12 (low: 0–2; moderate: 3–5; high: 6–12), higher scores representing worse health.

Physical and mental health status and quality of life are measured with the Short Form Health Survey-36 items (SF-36). SF-36 scores range from 0 to 100, where higher scores correspond to better health [36]. The SF-36 is a widely used, valid and reliable quality of life measure. It consists of 36 items and is categorised into nine subscales: physical functioning, role limitations caused by physical health problems, role limitations caused by emotional problems, social functioning, mental health, energy, pain, general health and health change. These subscales can be summarised into the two summary measures of the SF-36: the mental component summary (MCS) and the physical component summary (PCS) [37].

Health anxiety and illness behaviour are measured with the Illness Attitude Scale (IAS). The IAS, consisting of 29 items, assesses fears, beliefs and attitudes associated with hypochondriasis and abnormal illness behaviour and will be rated on a five-point Likert scale ranging from 0 (never) to 4 (most of the time) [38].

Illness beliefs are measured with the brief Illness Perception Questionnaire (IPQ-B) [39]. A higher score reflects a more threatening view of the illness. The IPQ-B is based on the revised IPQ-R [40] and designed to assess the cognitive and emotional representations of illness. It consists of nine items in total. Six items assess cognitive illness representations: consequences, timeline, personal control, treatment control, identity and comprehension of illness. One item reflects emotional representation, one item assesses a combination of emotional and cognitive representation: concern. The score will be rated on an 11-point scale, ranging from 0 (not at all) to 10 (very much). The last item is an open-question to assess causal representation.

The GP will be asked to report the total number of consultations of the patient in the year after the psychosomatic therapy.

All other medical consumption will be measured with the iMTA Medical Consumption Questionnaire (iMCQ) [41]. This questionnaire measures all relevant health care-related costs like outpatient visits at any medical specialist, hospitalisations and imaging procedures.

Productivity losses due to illness or recovery will be estimated based on patient-reported absences from paid labor measured with the iMTA Productivity Cost Questionnaire (iPCQ) [41, 42]. For all secondary outcome measures we will measure mean change from baseline at 4 and 12 months’ follow-up.

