**Fig. 1 Fig1:**
[figure not shown]
Schedule of enrolment, interventions and assessments. *PST* psychosomatic therapy; *CAU* care as usual; *PHQ-15* Patient Health Questionnaire 15-item somatic symptom scale; *PSFS* Patient Specific Functioning Scale; *iMCQ* iMTA Medical Consumption Questionnaire; *iPCQ* iMTA Productivity Cost Questionnaire; *NRS* numeric rating scale; *SF-36* Short Form Health Survey-36 items; *4DSQ* Four Dimensional Symptom Questionnaire; *GPE* Global Perceived Effect; *IAS* Illness Attitude Scale; *IPQ-B* Brief Illness Perception Questionnaire; *SRS-DV* Session Rating Scale Dutch version; *WAI-SF* Working Alliance Inventory short form; *1* only intervention group, directly after first session; *2* only intervention group directly after last session

We will perform a pragmatic randomised effectiveness trial with economic evaluation in primary care with patients aged 18–80 years who frequently, i.e. twice or more in the past months, consult their GP for MUS. Details regarding recruitment are presented below (see ‘Recruitment of study participants’ section). Patients will be individually randomised into intervention (psychosomatic therapy in addition to usual care) or control condition (usual care alone). The intervention (psychosomatic therapy) consists of 6 to 12 sessions, depending on number and severity of the patient’s symptoms, each of 30–45 min. Therapy will be delivered by a qualified psychosomatic therapist. The primary outcome measure will be functioning and disability measured with the Patient-Specific Functional Scale (PSFS) [24]. All patients will be followed for 1 year and will be asked to complete questionnaires at baseline and at 4 and 12 months’ follow-up. Participants in the intervention group will be referred to one of the 26 participating qualified psychosomatic therapists, physiotherapists or exercise therapists with a special interest in MUS, who receive a training for this study.

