## Methods: assignment of intervention

### Allocation and blinding

We will use Castor EDC for the online measurements and for randomisation of the participants [48]. Castor EDC uses a variable block randomisation method and randomly assigns participants to one of the two groups, the allocation ratio will be 1:1. The randomisation sequence is masked for study personnel. In order to balance the size of the intervention and usual care groups in each region, randomisation will be stratified according to regions (Amsterdam or Nijmegen). Patients will be included in either the intervention group or the usual care group based on the random allocation. The research assistant will give all patients a unique patient identification number, matching with the corresponding name to inform each participant about the allocation. All patients will be informed about the allocation by the research assistant by regular mail. Patients randomised to the psychosomatic therapy group will also be informed about the psychosomatic therapy by telephone by the research assistant and will receive a referral from their GP to one of the psychosomatic therapists participating in this study. If patients are randomised to the usual care group, they will be offered to receive psychosomatic therapy after completion of the study if still indicated. The research assistant will inform all GPs about the inclusion and allocation of their patients by regular mail or secure e-mail.

Since psychosomatic therapy is a face-to-face intervention, patients and therapists cannot be blinded to allocation. The data analysts will not be blinded to treatment assingments, as this would be unfeasible because they are also involved in data collection.

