#### Economic evaluation

##### Cost-effectiveness of the intervention

We will conduct an economic evaluation from a societal perspective in accordance with the Dutch guidelines for economic evaluation [50]. Effectiveness is presented in terms of quality-adjusted life years (QALYs). QALYs are a combination of quality of life and survival, where quality of life is expressed as a utility score between 0 (representing death) and 1 (representing perfect health). Utility scores will be calculated through the SF-6D, which is a well-known classification for describing health derived from a selection of SF-36 items [36, 51]. Based on the SF-6D health state, each patient is assigned a utility score at three time points (baseline, 4 months, 12 months), using tariffs from the general population. QALYs will be calculated using the area-under-the-curve method, using the utility scores at baseline, 4 months and 12 months.

Since the economic evaluation will be performed over a time horizon of 1 year, costs and effects will not be discounted.

The cost analysis consists of two main parts. First, at patient level, volumes of care related to the care of patients with MUS will be measured by means of the iMCQ and iPCQ [41, 42]. The second part of the cost analysis consists of determining the cost prices for each volume of consumption. The standard cost prices from the ‘Dutch Guidelines for Cost Analyses’ [52] will be used to determine the cost prices for each volume of consumption. For units of care where no standard prices are available real cost prices will be determined. To obtain total costs, resource use will be multiplied with the cost prices. Productivity losses will be valued by means of the friction cost method [53–55].

Differences in costs and QALYs per patient between the two treatment arms will be calculated, according to the ITT and the per-protocol principle. Patients in the intervention group that have completed at least four sessions will be used for the per-protocol analysis. Where relevant, incremental cost-effectiveness ratios (ICERs) will be calculated to reflect the extra costs per QALY gained.

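### GP consultations are counted from the end of therapy, so controls and non-starters have no defined window and the arms are not compared like for like

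*Protocol article*

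**What the plan says.** All references are to the Protocol article.

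- **Secondary outcomes**, on the count: "The GP will be asked to report the total number of consultations of the patient in the year after the psychosomatic therapy". The same section closes with a rule for the whole set: "For all secondary outcome measures we will measure mean change from baseline at 4 and 12 months".
- **Study design**, on follow-up: "All patients will be followed for 1 year and will be asked to complete questionnaires at baseline and at 4 and 12 months". The intervention "consists of 6 to 12 sessions, depending on number and severity" of symptoms. Controls have usual care alone.
- **Psychosomatic therapy**: therapists may vary the intensity, frequency and order of the elements.
- **Allocation and blinding**, on controls: "they will be offered to receive psychosomatic therapy after completion of the study if still indicated".
- **Statistical analysis**: the primary analysis is by intention to treat and includes everyone randomised.
- **Sample size and power calculation**: the planned size is said to suffice also for number of consultations, with a minimally relevant difference (mrd) of 3 and a standard deviation (SD) of 4.
- **Cost-effectiveness of the intervention**: "Since the economic evaluation will be performed over a time horizon of 1 year, costs and effects will not be discounted". Volumes of care come from the iMCQ and iPCQ.

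The abstract lists consultation frequency as a secondary outcome, and the Introduction includes reducing it in the aims. No section gives a counting window for the control arm.

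**The concern.** A count compared between randomised arms needs a window that starts and ends by the same rule in both. Here the starting point is the end of a treatment that only one arm receives. Someone extracting the data would have to invent a start date for every control and for every intervention patient who never attended.

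For treated patients the start date is itself a post-randomisation event. The number of sessions depends on the number and severity of symptoms, so sicker patients may have later windows. Their consultations during therapy go uncounted.

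At stake is a named between-arm outcome with its own power statement. Patients enter because they consult often, so attendance may fall back in both arms without any treatment effect. If it does, a later window in one arm would show fewer visits for reasons unrelated to the therapy.

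**Working it through.** **Step 1. The plan's own figure.** Inputs from Sample size and power calculation: difference 1, SD 2, alpha 0.05 (taken as two-sided), power 0.80, dropout 20%.

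- n per arm = 2 × (1.960 + 0.842)² × 2² / 1² = 62.8, rounded up to 63.
- 63 / 0.80 = 78.75, rounded up to 79. This reproduces the stated 79.
- For consultations with 63 evaluable per arm: standard error = 4 × √(2/63) = 0.713. Then 3 / 0.713 = 4.21 and 4.21 − 1.96 = 2.25, so power is about 0.99.

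The power statement for consultations is sound. The problem is what is being counted.

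**Step 2. Apply the window as written.**

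| Patient | Start of window | Consequence |
|---|---|---|
| Control | None within the trial | Count undefined |
| Allocated to therapy, never starts | None | Count undefined, though the patient is in the intention-to-treat set |
| Treated, therapy ends d months after randomisation | Month d, varying by patient | Months 0 to d omitted; window ends at month 12 + d, after the 1-year follow-up |

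A single annual total also cannot yield a value at 4 months, so it cannot satisfy the rule on change at 4 and 12 months.

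**Step 3. Illustrate the size with no treatment effect.** Suppose controls are counted over months 0–12 and treated patients over months d to 12 + d. Both arms share one rate, r(t) = f + (10.2 − f)·exp(−kt) per year, with t in years and k = ln 2 / half-life. The spurious difference is

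Δ = [(10.2 − f)/k] × (1 − e^(−k)) × (1 − e^(−kd)), with d in years.

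The starting rate of 10.2 visits a year is the Introduction's figure for persistent frequent attenders. The plateau f (5 to 9), the half-life (3 to 12 months) and d (2 to 6 months) are assumptions; the article states none of them.

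With a half-life of 6 months (k = 1.386):

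| Plateau f | d = 2 months | d = 4 months | d = 6 months |
|---|---|---|---|
| 9 | 0.13 | 0.24 | 0.32 |
| 7 | 0.36 | 0.64 | 0.87 |
| 5 | 0.58 | 1.04 | 1.41 |

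- Largest value: f = 5, half-life 6 months, d = 6 months: (5.2/1.386) × 0.75 × 0.50 = 1.41.
- Smallest value over the whole grid: f = 9, half-life 12 months, d = 2 months: (1.2/0.693) × 0.50 × 0.109 = 0.09.
- Constant rate (f = 10.2): Δ = 0.

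The range is therefore about 0.1 to 1.4 visits in favour of therapy, or 0.09/3 = 3% to 1.41/3 = 47% of the mrd. With 63 per arm and SD 4, the chance of a significant result in favour of therapy when there is no effect is 0.034 at the mild end and 0.505 at the extreme end, against a nominal 0.025.

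**The case against.** The strongest reply is that the phrase is a loose name for the follow-up year in a condensed article. "All patients will be followed for 1 year" points that way, as does the rule placing all secondary outcomes at 4 and 12 months. So does the Trial status section, where recruitment starts in January 2019 and follow-up assessments are expected to end in January 2021. This may be what was meant. No section says so, however, and a GP asked the question literally could not answer it for a control patient. The reply softens the point without removing it.

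Four stronger readings might be inferred, and the article does not support them.

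- *The comparison is shown to be biased.* The control window is unstated, so neither size nor direction can be fixed. Attendance may fall, but nothing in the article establishes that it will. The 10.2 figure describes persistent frequent attenders, whereas Study design defines frequent attendance as two or more visits in the past months.
- *The treated arm loses about 3 visits, as much as the mrd.* That requires stopping the treated window at month 12 and comparing it, without adjusting for exposure time, with 12 months in controls. The text specifies a full year.
- *Intention to treat is abandoned.* The article analyses everyone randomised and seeks follow-up regardless of compliance. Non-starters lack an anchor because of the same wording gap.
- *The control window runs into the later offer of therapy.* No section extends the control window, and the offer comes only after study completion.

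A link to the costs is also only an inference. Secondary outcomes assigns all other medical consumption to the iMCQ, which suggests that GP visits come from the GP report, but the economic section names only the iMCQ and iPCQ.

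**Conclusion.** The point holds as a defect of definition. As written, the count has no start date for controls or non-starters, covers a shifted period in treated patients and contradicts two other statements in the article. The resulting comparison of consultation frequency is open to bias if attendance changes over time. The 0.1 to 1.4 visits from the illustration assume that both arms get a full year, that therapy lasts 2 to 6 months and that the underlying rate declines. With a constant rate the spurious difference disappears, although consultations during therapy would still be missing from one arm only.

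The damage is confined to one secondary outcome and possibly to GP visits in the cost analysis. The primary analysis of the Patient-Specific Functional Scale and the 79 per arm stand.

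**What to change.** Replace the sentence with a definition along these lines: the number of GP consultations from randomisation to 12 months, in both arms and for all randomised patients, taken from the GP record, with the equal-length period before randomisation as baseline.

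Two consequential edits follow:

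- Exempt this count from the rule on change from baseline at 4 and 12 months.
- State whether GP visits in the 1-year cost analysis come from the GP record or from the iMCQ, and use the same window there.

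The choice of count model can be left to the statistical analysis plan.

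The cost is a few sentences and a reworded data request to the GPs. The visits are already in the practice records, and the window closes with the planned follow-up. The sample size does not change: 63 evaluable patients per arm still give power of about 0.99 for a difference of 3 with SD 4.

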**Methods:**

A randomised effectiveness trial with an economic evaluation in primary care with 158 patients aged 18 years and older who are frequently consulting their GP with MUS. Patients will be assigned to psychosomatic therapy in addition to usual care or usual care only. Psychosomatic therapy is a multi-component and tailored intervention, aiming to empower patients by applying psycho-education, relaxation techniques, mindfulness, cognitive approaches and/or graded activity. Patients assigned to the psychosomatic therapy receive 6 to 12 sessions of psychosomatic therapy, of 30–45 min each, delivered by a specialised exercise or physical therapist.

Primary outcome measure is patient-specific functioning and disability, measured with the Patient-Specific Functional Scale (PSFS). Secondary outcome measures are symptom severity, consultation frequency and referrals to secondary care, patient satisfaction, quality of life and costs. Assessments will be carried out at baseline, and after 4 and 12 months.

An economic evaluation alongside the trial will be conducted from a societal perspective, with quality-adjusted life years (QALYs) as outcome measure. Furthermore, a mixed-methods process evaluation will be conducted.

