### Sample size and power calculation

The main aim of our study is to establish whether, compared to usual care, psychosomatic therapy improves daily functioning, disability and symptoms, while reducing costs.

Calculations of sample size are based on a minimally relevant difference (mrd) between the two arms of 1 point on the PSFS (range 0–10) [32], with a standard deviation (sd) of 2 points, with an alpha of 0.05 and a power of 0.80. With an estimated dropout rate of 20% after 1 year at least 79 patients per treatment arm need to be included. With this sample size, we can also detect differences in perceived symptom severity (measured on a visual analogue scale (VAS); mrd = 1.3; sd = 2.6) and number of consultations (mrd = 3; sd = 4).

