### Recruitment of study participants

The patients will be recruited from general practices participating in the Academic Network of General Practices of the VU Medical Center (ANH-VUmc), the Academic General Practices Network Academic Medical Center (AHN-AMC) and the Radboud University Medical Center Academic General Practices Network (Radboudumc-AHN). If the number of inclusions from these networks of general practices proves to be insufficient we will approach other general practices in the Netherlands (in and around Amsterdam and Nijmegen).

Eligible patients will be identified by a search strategy that selects from the electronic medical records those patients (aged 18 to 80 years) who visited their GP frequently over the past 2 years with MUS, based on a list of 23 unexplained physical complaints composed by Robbins et al. [27]. Patients who visited their GP twice or more in the past months with one or more Robbins List symptoms are eligible. Table 1 presents the Robbins List with 23 physical complaints. The GP will screen the selected list of this frequently attending group patients for potential exclusion criteria and/or other pertinent reasons for not inviting them, such as a terminal disease or insufficient understanding of the Dutch language. In addition to the search strategy, participating GPs will be asked to enrol eligible MUS patients who are not present on the selected list. The identified and screened potential participants not meeting exclusion criteria will be approached by their GP who sends them a package containing a letter with brief information about the study, the PHQ-15, a brief consent form to receive more information about the study and an addressed return envelope. The PHQ-15 is a frequently used and validated questionnaire about physical symptoms [29]. It consists of 15 items, each of which can be scored from 0 (‘not bothered at all’) to 2 (‘bothered a lot’), which results in a total score ranging from 0 to 30. Higher scores indicate higher somatic symptom severity. Scores of 5, 10 and 15 represent cut-off points for low, medium and high somatic symptom severity, respectively [28].

**Table 1 Tab1:** Symptoms from the Robbins List [27]

1. Back pain	
2. Joint pain	
3. Extremity pain	
4. Headaches	
5. Weakness	
6. Fatigue	
7. Sleep disturbance	
8. Difficulty concentrating	
9. Loss of appetite	
10. Weight change	
11. Restlessness	
12. Thoughts slower	
13. Chest pain	
14. Shortness of breath	
15. Palpitations	
16. Dizziness	

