A strength of our study is that the psychosomatic therapy is a well-accessible intervention already delivered in primary care by physical therapists with special interests in MUS. Psychosomatic therapy has an integral approach, focussing on physical, psychological and psychosocial factors; therefore, the intervention is possibly more appropriate for patients who decline CBT. Furthermore, the guideline on the management of MUS of the Dutch College of General Practitioners [30] is very positive about psychosomatic therapy, although the evidence for the effectiveness of this therapy is still lacking. All participating psychosomatic therapists will participate in an intensive training (e-learning and meetings) about the content of the standardised treatment protocol and education in MUS. By this training we will minimise the differences in the psychosomatic therapy delivered by the psychosomatic therapists [66]. In addition, we will conduct a process evaluation through interviews with the participating therapists to explore the possible facilitators and barriers of the psychosomatic therapy from the therapists’ perspective. The findings will improve or refine the intervention. Another strength of our study is the 12-month follow-up measurement as it will result in data being obtained about long-term (cost)-effectiveness of the intervention. The aim of the psychosomatic therapy is to give patients insight into the interaction of their psychosocial factors with their somatic complaints and thus to empower patients to regain control over their own health, focussing on self-management and behaviour changes. Therefore, a 12-month follow-up is appropriate, since the process of behavior change will take at least 6 months [67].

A possible limitation to our study is the exclusion of patients who do not have sufficient understanding of the Dutch language. About 13% of the Dutch population are non-Western immigrants and their offspring. A proportion of them has insufficient command of the Dutch language; therefore, a part of the potential target population for this intervention will probably have to be excluded. Another limitation to our study is that blinding of patients, therapists, GPs and researchers to treatment allocation is not possible, due to the nature of the intervention.

In conclusion, if proven cost-effective, psychosomatic therapy would provide a valuable additional treatment option for adult patients with MUS.

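### The GP consultation count comes from a GP who knows the allocation, and the protocol does not tie it to the practice record by a fixed rule

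*Protocol article*

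**What the plan says.** The abstract lists the outcome: "Secondary outcome measures are symptom severity, consultation frequency and referrals to secondary care". The Secondary outcomes section gives its source: "The GP will be asked to report the total number of consultations of the patient", for the year following the therapy. It does not say how the GP arrives at the total or which contacts count.

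Allocation and blinding states: "The research assistant will inform all GPs about the inclusion and allocation of their patients by regular mail or secure e-mail". The Discussion names this as a limitation: "blinding of patients, therapists, GPs and researchers to treatment allocation is not possible". Allocation and blinding adds that the data analysts also know the assignments and take part in data collection.

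The practice records are already in use. Recruitment of study participants states: "Eligible patients will be identified by a search strategy that selects from the electronic medical records those patients", the criterion being frequent GP visits over the past 2 years with complaints on the Robbins List. GPs may also enrol suitable patients whom the search did not list.

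The sample size section says that the planned sample can also detect a difference in the "number of consultations (mrd = 3; sd = 4").

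**The concern.** Most outcomes in this trial are patient questionnaires, and no change of design protects those from knowledge of the arm. The consultation count is different, because it can be obtained by a rule that ignores the arm. As written, it is one total supplied by someone who has been told the allocation. If the GP has to decide whether telephone contacts, home visits or administrative contacts count, that decision may be made with the arm in mind. No later blinded step would catch a difference.

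At stake is the credibility of a between-arm difference in consultations. The Discussion section of the abstract expects consultation frequency to fall, and the sample size section makes a specific claim about detecting such a fall.

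**Working it through.** **Inputs.** PSFS difference 1, SD 2, alpha 0.05 (taken as two-sided; the article does not say), power 0.80, 20% dropout, 79 per arm; consultations difference 3, SD 4 (all from Sample size and power calculation). The figure of 10.2 visits per year for persistent frequent attenders is from the Introduction and serves only as a scale.

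**1. The plan's own figure.** n per arm = 2(1.960 + 0.842)² × 2²/1² = 62.8, so 63. Allowing for dropout, 63/0.80 = 78.75, so 79. This matches.

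**2. The claim about consultations.** n per arm = 2(1.960 + 0.842)² × 4²/3² = 27.9, so 28. With 63 completers per arm:
- SE = 4 × √(2/63) = 0.713
- power = Φ(3/0.713 − 1.960) = 0.988

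The claim is correct. No figure in the plan is disputed, and the fix changes no sample size.

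**3. What a reporting shift would do (illustration).** Suppose there is no true difference and GPs' reports differ between arms by b consultations on average. The two-sided rejection probability is Φ(−1.960 + b/0.713) + Φ(−1.960 − b/0.713).

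| Assumed shift b | b as share of 3 | Rejection probability |
|---|---|---|
| 0.25 | 8% | 6.4% |
| 0.5 | 17% | 10.8% |
| 1.0 | 33% | 28.9% |

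The observed difference needed for significance is 1.960 × 0.713 = 1.40.

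**4. Scale.** If 5% or 10% of contacts were left out in one arm only, at 10.2 visits per year, the shift would be 0.51 or 1.02 consultations, giving about 11% or 30%. Both the omission rates and the use of 10.2 for this sample are assumptions.

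**5. The text.** The GP is the source, the GP knows the arm, and the record is accessible. No sentence says that the total is taken from the record or checked against it, and none says that it is not. The risk is therefore open in the plan as stated, and its presence in the data cannot be inferred.

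**The case against.** The strongest reply is that the text does not describe a judgement or a recollection. A practice asked for a yearly total may simply read it from the record, and the full protocol or the case record form may say so. A count is among the less subjective outcomes here, it is secondary, and the article discloses that GPs are not blinded. Much of this stands. It limits the point to an open risk. It does not remove it, because the article names a source, the GP's report, and a rule-based source is within reach. Disclosing that GPs cannot be blinded does not explain why the count has to depend on their report.

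Four stronger readings are tempting and lack support:
- **That GPs have an interest in the result.** Nothing in the article says so. Referral of intervention patients follows randomisation and shows no preference.
- **That bias is present, of a known size.** The shifts above are assumed. Even the largest, 1.0, is below the 1.40 needed for significance and is a third of the stated difference. The 10.2 visits per year describes persistent frequent attenders in a cited source, not this trial's patients.
- **That the recruitment search can be rerun unchanged.** It selects on Robbins List complaints, whereas the outcome is all consultations. It also may not list patients whom the GP enrolled directly.
- **That extraction makes the count independent of the GP.** Practice staff who know the arm still make the entries, and unblinded patients and GPs may change how often they actually meet.

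**Conclusion.** The point holds as a design choice that can be improved cheaply. The consultation count is reported by a GP who knows the allocation, and the article sets no rule linking it to the record, so differential counting is possible and largely avoidable. Its size and direction are unknown. The error rates of about 6%, 11% and 29% rest on assumed shifts of 0.25, 0.5 and 1.0 consultation, SD 4, 63 completers per arm, a normal approximation and no true effect; they show sensitivity and estimate nothing about this trial. The primary outcome and the sample size are unaffected. The change should be made, but the trial's main conclusion does not depend on it.

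**What to change.** Amend the sentence on GP consultations in Secondary outcomes to state that:
- the count is extracted from the practice's electronic record;
- one fixed definition of a consultation applies, saying whether telephone, home and administrative contacts count;
- one calendar window runs from randomisation in both arms (the present window starts from the therapy, which gives usual-care patients no starting date);
- extraction is identical in both arms and is run on study numbers without the allocation;
- a GP report is used only where extraction fails, and those patients are flagged.

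The recruitment search has to be adapted to count all consultations and to cover patients enrolled directly by the GP and any practices added later.

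The cost is modest practice and data-handling work, partly offset by no longer asking every GP for a total, and consent wording that covers extraction. Recruitment, treatment and sample size do not change. The benefit is limited to reporting bias: any effect of unblinding on actual consulting, or on how contacts are recorded, remains and should be acknowledged when the result is reported.
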